#### Blinding

Due to the behavioral nature of the intervention, neither participants nor therapists and ITAs who interpret the therapy can be blinded. However, the group allocation of the subjects will be concealed from the independent outcome assessors who will conduct the follow-up interviews. At the beginning of the follow-up interviews, participants will be instructed not to reveal any information related to the group that they have been assigned to or regarding the therapeutic process. After the completion of all diagnostic instruments of the follow-up interview, the independent assessors will complete a questionnaire asking whether any information regarding group allocation was revealed in the diagnostic interview. Cases of premature unblinding will be documented and reported.

#### Measures taken to prevent bias in assessment

The diagnostic interviews will be conducted by specially trained assessors. As the CAPS-CA-5 [33] serves as the primary outcome of the study, assessors are extensively trained in this instrument. During the trial, all interviews will be videotaped and a random selection of 10% per site will be checked and rated by an independent evaluator to assess interrater reliability of the CAPS-CA-5.

#### Treatment fidelity

Treatments with KIDNET will be conducted by expert clinicians (minimum bachelor’s degree) specialized in the field of psychotraumatology. All study therapists receive a training in KIDNET which includes a 2-day basic training including the theoretical background of the treatment, the practical implementation of KIDNET, case demonstrations, practical exercise and role-plays in small groups under the supervision of experienced KIDNET therapists. This initial training is followed by an advanced training which includes the discussion and review of test cases. Furthermore, treatment fidelity during the trial will be assured by external NET case consultation with experienced NET therapists after at least every fourth therapy session as well as regular supervision and intervision meetings at the study centers. The frequency of supervision and intervision meetings at the sites will be recorded throughout the study. In addition, all sessions will be videotaped and a random selection of 10% per site will be checked by independent raters for consistency with the treatment manual. Finally, 10% of the therapy session sheets (which assess the date, duration, main topics covered in the session, as well as difficulties in the KIDNET process) of all centers will be reviewed. Observed inconsistencies with the treatment manual will be documented, but do not constitute an exclusion criterion for the trial.

#### Measures taken to avoid attrition bias

In order to avoid systematic drop-out from the study, participants will receive compensation of 20€ in the form of a voucher for each follow-up interview. Furthermore, the inclusion of the caregivers and ITAs in the therapeutic process is intended to increase the cultural acceptance of the intervention as well as the reliability of the children and adolescents to show up for the sessions and diagnostic interviews. Finally, we will analyze all trial participants as randomized (intention-to-treat analyses).

### Data management

Data will be collected at the study centers according to the General Data Protection Regulation (GDPR). The PI will appoint and supervise a Data Management Team (DMT) responsible for all aspects related to data storage, data integrity and data monitoring during the project period. Data storage and transfer will be conducted exclusively in an encrypted manner.

The centers will transfer the pseudonymized encrypted data to a secured server accessible by the DMT. The DMT will create a merged, pseudonymized dataset only accessible by themselves which will be stored for the project duration. Checks for completeness as well as range checks will be conducted to ensure data integrity. Furthermore, the DMT will perform at least one site-monitoring per year at each participating center where access will be granted to source documents in order to check for completion of informed consent sheets and consistency with the entered data.

Statistical analyses will be conducted by the independent certified biostatistician [name], who will also supervise the DMT in accordance with the GDPR. For long-term storage, the anonymized dataset (after deletion of the code list and database lock) will be stored in the Bielefeld University data repository and provided to external scientists upon request for further analysis.

## Statistics

### Power analysis and sample size calculation

The Ruf et al. pilot study [26] achieved a treatment effect size of 1.9 for NET and 0.3 for the waiting-list control group. However, we expect that the contrast will be smaller for this study, as we will have an active control condition and will provide detailed information to children and adolescents from the TAU condition on how to seek treatment in the regular health care system. Therefore, we base the effect size calculation at a conservative estimation of a between-group effect size of *d* = 0.6. To test the hypothesis that a treatment with KIDNET is more effective than TAU, with a one-sided alpha level set at 0.05 and a power level of 0.8, we need to enroll *N* = 72 subjects (*N* = 36 per group) into the present study. Once randomized, loss to follow-up was small (generally lower than 5%) in the Ruf et al. study [26] as well as in other NET studies [50]. Most importantly, as the main analysis of the primary outcome measure will be calculated using a mixed-effects model, all randomized cases can be included in the statistical analyses. Therefore, the intended sample size of *N* = 80 will be sound to answer the research questions of the trial.

### Data analyses

The confirmatory analysis of this study will be calculated as a mixed-effects model with the CAPS-CA-5 score as the outcome variable. Mixed models are especially suited for longitudinal studies as they can account for serial correlation within participants, are relatively robust to randomly missing data, and can incorporate certain nonrandom missing data without biasing model estimates. In detail, participants will be modeled as a random factor (including random intercepts or random intercepts and slopes), while time and intervention (KIDNET vs. TAU), as well their interaction, will be modeled as fixed factors. The hypothesis that KIDNET is superior to TAU in the treatment of PTSD will be evaluated by the significance test of the interaction effect time × intervention.

In case of a significant interaction effect, two planned general linear hypotheses will be calculated as post-hoc tests for linear mixed-effect models in order to test between-group differences at t_2_ and t_3_. One-sided *p* values will be adjusted for multiple comparisons following the Holm procedure.

We will perform an intention-to-treat analysis; that is, all trial participants will be analyzed as randomized, even if they discontinue treatment or are unavailable for one or both of the follow-up interviews. The between-group effect size (Cohen’s *d*) will be calculated at each follow-up assessment (t_2_ and t_3_). The intention-to-treat analysis will be supplemented by a modified intention-to-treat analysis which will include only those participants who participated in at least one post-randomization diagnostic interview. Furthermore, participants who were randomized to KIDNET will be included only if they participated in at least one KIDNET therapy session.

Continuous secondary outcome measures are analyzed in the same way. In the absence of a valid cut-off score for clinically significant change or treatment response of the CAPS-CA-5, the rate of subjects with clinically significant improvement as well as worsening based on the RCI will be compared between groups using Fisher’s exact tests at the follow-up assessments t_2_ and t_3_, separately. For this purpose, the RCI will be calculated based on the pre-treatment scores of the study sample following the suggestion of Jacobson and Truax [39]. Missing values due to premature withdraw will be considered as treatment failure (classified as no response).

In addition, in case of significant treatment effects, center effects regarding the primary efficacy endpoint are investigated. For this purpose, the change in CAPS-CA-5 at t_3_ (compared to baseline t_1_) are analyzed exploratively using a mixed-effects model that includes participants as a random factor and center, intervention and center × intervention as fixed factors. The significance level will be set at 0.05 for all analyses.

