## Methods

### Trial design

YOURTREAT is a randomized controlled, rater-blinded, two-arm, multi-center, superiority trial with a 1:1 allocation ratio to two parallel groups. Individuals who are screened eligible for the trial will participate in a comprehensive diagnostic interview (t_1_). Among other information (detailed below), this structured interview will assess the diagnosis of PTSD according to the *Diagnostic and Statistical Manual of Mental Disorders, 5th edition* (*DSM-5*). We expect that we will have to interview approximately *N* = 220 children and adolescents (*N* = 55 per site) in order to identify 80 participants (*N* = 20 per site) who fulfill the diagnostic criteria of PTSD. These PTSD patients will be immediately randomized to one of the two arms of the trial; KIDNET or TAU. For individuals included in the KIDNET group, the treatment starts within 1 month after the diagnostic interview and should be terminated at the latest 5 months after randomization. For the beginning and ending of the NET, a tolerance window of 1 week is considered acceptable. Deviations from this time window will be reported. Individuals assigned to TAU will be informed about treatment and counseling options within the local general health care system immediately after the diagnostic interview.

Six months after the diagnostic interview and the randomized group allocation, the first follow-up interview will take place (t_2_). This time point was selected in order to assure a minimum time interval of 1 month between the end of KIDNET and the first follow-up interview. In this way, the diagnostic interview which measures PTSD symptoms in the past month, will not be biased by the experience of symptoms during exposure therapy. The second follow-up interview (t_3_) is scheduled for 12 months after randomization. For the appointments of the follow-up interviews, a tolerance window of ±  2 weeks is considered acceptable. Deviations from this time window will be reported. See Fig. 1 for a schematic overview of the participant flow through the trial. The study protocol was written following the Standard Protocol Items: Recommendations for Interventional Trials (SPIRIT) Statement 2013 [32]. See Additional file 1 for the SPIRIT Checklist. The trial was registered at the German Clinical Trials Registry (Deutsches Register Klinischer Studien; DRKS) on 15 May 2019 (ID: DRKS00017222).

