### Outcomes of the trial

#### Primary outcome

The primary outcome of the trial will be the change in PTSD symptom severity from the diagnostic interview before treatment initiation (t_1_) to the follow-up assignments (t_2_ and t_3_). PTSD symptoms will be measured at each assessment by a structured clinical interview using the Clinician-administered PTSD Scale for DSM-5 – Child/Adolescent Version (CAPS-CA-5) [33]. The CAPS-CA-5 represents the “gold standard” for the assessment of PTSD and will be administered by trained psychologists with the help of ITAs who can interpret, if required. In order to standardize the translation of the ITAs, we will translate the CAPS-CA-5 into the most common languages spoken by the patients, e.g., Arabic, Kurdish, Dari and Farsi. Treatment response will be defined as the results of a mixed linear model with the CAPS-CA-5 total symptom score as outcome variable and time and intervention group as well as their interaction as fixed factors. Furthermore, group means (KIDNET vs. TAU) will be compared and the between-group effect sizes (Cohen’s *d)* will be calculated at each follow-up assessment.

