### Measures against bias

#### Randomization

Subjects will be randomly allocated to the two arms of the trial using block-permuted randomization stratified by center based on computer-generated lists that will be provided by the independent statistician. Participants who fulfill the inclusion criteria, including a diagnosis of PTSD, will be immediately assigned to the interventions. Diagnosticians for the baseline diagnostic interview will receive a sequentially numbered, sealed, opaque envelope which will reveal group allocation in case the subject meets the diagnostic criteria for PTSD. The random sequence that determines treatment allocation is kept in a sequence of enumerated sealed envelopes that are provided to the centers. The envelopes will remain sealed to ensure concealment of the sequence of treatment allocations from the research team, assessors and the therapists. At the moment that a patient is assigned to the trial the single corresponding envelope is opened to reveal the allocation of the therapist. Block sizes vary randomly and will not be disclosed in order to assure concealment.

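### The confirmatory model leaves baseline CAPS-CA-5 unadjusted and omits center, so it gives up precision and lets chance baseline differences move the change and level contrasts in opposite directions

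*Protocol article*

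**What the plan says.** All references are to the Protocol article.

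- **Outcome and fixed effects.** Primary outcome defines the endpoint as change in CAPS-CA-5 from t1 to t2 and t3. There and in Data analyses the fixed factors are listed as time, intervention and their interaction, and superiority is judged by the interaction. For that test to address efficacy, t1 must be one of the outcome occasions. The intervention main effect then lets the arms differ at t1.
- **Random part.** Data analyses offers two options without a rule for choosing: "participants will be modeled as a random factor (including random intercepts or random intercepts and slopes), while time and intervention".
- **After the gate.** If the interaction is significant, arm differences at t2 and t3 are tested one-sided with Holm adjustment. Primary outcome adds that "group means (KIDNET vs. TAU) will be compared and the between-group effect sizes" are calculated at each follow-up.
- **Center.** Randomization is "block-permuted randomization stratified by center" (Randomization). In the analysis, center appears only in an exploratory model of change at t3, run only after a significant treatment effect.
- **Sample size.** Power analysis and sample size calculation assumes a "between-group effect size of *d* = 0.6", "with a one-sided alpha level set at 0.05 and a power level of 0.8", and concludes "we need to enroll *N* = 72 subjects (*N* = 36 per group"). The target of 80 is split equally (Trial design: "superiority trial with a 1:1 allocation ratio to two parallel groups").

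**The concern.** With t1 in the outcome vector and free arm means at t1, the interaction compares raw changes, while the follow-up contrasts and Cohen's d compare raw levels. Neither uses the baseline score to remove between-patient variation. With 80 patients, that precision can be recovered without new data.

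The two quantities also respond in opposite ways to a chance difference at t1. If KIDNET patients happen to start higher, the change contrast flatters KIDNET and the level contrast penalizes it. The gate and the reported effect can then point differently for a reason unrelated to treatment.

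Two smaller points belong to the same model. The stratification factor is left out. The random structure is an open choice, and random intercepts alone impose equal variances and equal correlations over time. Because entry requires a PTSD diagnosis, the t1 variance may well be smaller than at follow-up.

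**Working it through.** **Inputs.** From the article: d = 0.6, one-sided alpha 0.05, power 0.80, 36 per arm required, 40 per arm intended, four centers. Not given, hence assumed: baseline–follow-up correlation rho, the ratio s of t1 SD to follow-up SD, and the center ICC.

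**1. The plan's own figure.** An exact one-sided two-sample t-test with d = 0.6 needs 36 per arm (power 0.809), so N = 72 reproduces. At 40 per arm the power is 0.845 (0.85 by normal approximation). This calculation is for a single comparison that makes no use of baseline.

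**2. Variance of each contrast at one follow-up visit, in units of the follow-up variance.**
- Level: 1
- Change: 1 + s² − 2·rho·s, which is 2(1 − rho) when s = 1
- Baseline-adjusted: 1 − rho²

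Ratios to the adjusted variance with equal SDs (s = 1):

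| rho | change, 2/(1+rho) | level, 1/(1−rho²) |
|---|---|---|
| 0.3 | 1.54 | 1.10 |
| 0.5 | 1.33 | 1.33 |
| 0.7 | 1.18 | 1.96 |

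Ratios for the change contrast with a compressed t1 SD:

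| s | rho | (1 + s² − 2·rho·s)/(1 − rho²) |
|---|---|---|
| 0.6 | 0.3 | 1.00/0.91 = 1.10 |
| 0.6 | 0.4 | 0.88/0.84 = 1.05 |
| 0.7 | 0.3 | 1.07/0.91 = 1.18 |
| 0.7 | 0.4 | 0.93/0.84 = 1.11 |

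The equivalent loss of patients on the change contrast is 1 − 1/ratio: 35%, 25% and 15% in the first table, but about 5–15% in the second. The level ratio does not depend on s; at rho 0.3–0.4 it is 1/0.91 = 1.10 to 1/0.84 = 1.19.

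**3. Power at 40 per arm for one visit, s = 1.** Power is Φ(0.6·√(20/V) − 1.645), with V the variance from step 2.

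| rho | level | change | adjusted |
|---|---|---|---|
| 0.3 | 0.85 | 0.73 | 0.88 |
| 0.5 | 0.85 | 0.85 | 0.93 |
| 0.7 | 0.85 | 0.97 | 0.98 |

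These are single-visit figures, not the power of the joint interaction test.

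**4. Chance imbalance.** The standard error of the t1 difference is √(2/40) = 0.224 SD. A difference beyond 0.2 SD arises in 37% of trials and beyond 0.3 SD in 18%. With s = 1, a 0.2 SD imbalance shifts the level contrast by 0.2·rho = 0.06, 0.10 or 0.14 SD at rho 0.3, 0.5 or 0.7. It shifts the change contrast by 0.2·(rho − 1) = −0.14, −0.10 or −0.06 SD. For general s the change shift is proportional to rho − s, so the directions are opposite whenever rho < s.

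**5. Center.** A constant center effect cancels from the interaction. For the level contrasts, the unadjusted one-sided error is 1 − Φ(1.645/√(1 − ICC)): 4.8% at ICC 0.02 and 3.7% at ICC 0.15, which is conservative. Adjustment raises power from 0.853 to 0.857 and from 0.870 to 0.897 respectively, a gain of 0.4 to 2.7 points.

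**6. Random intercepts only.** This was simulated under the null with 40 per arm and complete data. With the t1 SD at roughly 0.6–0.75 of follow-up, a single t2 or t3 level contrast taken alone runs at about 6–8% one-sided. The interaction test runs at about 5–6%. The chance that any Holm-adjusted level claim passes after the interaction gate is about 1.5–2.0% (2.3–3.2% if the contrasts are taken on change).

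**The case against.** Much of the case for the plan stands.

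- **Validity.** Over randomizations both contrasts are unbiased, and chance imbalance is already in their standard errors. The plan is not invalid.
- **Error rate.** A reader might infer from the 6–8% figure that the trial's one-sided error exceeds 5%. The article does not support that: the t2 and t3 tests run only after a significant interaction and are Holm-adjusted, and that sequence stays well below 5% under the global null. What remains is a risk for a single contrast taken alone.
- **Size of the loss.** A reader might put a 15–35% loss of patients next to the compressed-baseline argument. The two rest on different assumptions: 15–35% needs equal SDs, and under compression the loss is about 5–15%.
- **Power.** A reader might conclude that the trial is underpowered. N = 72 reproduces for an unadjusted comparison, and the single-visit change contrast drops below 0.80 only at low correlation with near-equal SDs.
- **Two quantities.** The article assigns the superiority hypothesis to the interaction alone, which matches its change endpoint. The later tests are post hoc and could be coded as contrasts of interaction terms; the level reading is the natural one but is not spelled out.
- **SAP content.** Covariance structure and degrees of freedom often sit in an SAP. Here, however, the article itself lists the fixed factors in full and writes the either/or for the random part.

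**Conclusion.** The point holds as one of efficiency and of an unsettled specification. As listed, the confirmatory model makes no use of baseline as an adjuster and omits the stratification factor. Its gate and its follow-up contrasts are both less precise than they need be and respond in opposite directions to chance imbalance.

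The size depends on values the article does not report. The change-contrast variance is 1.18–1.54 times the adjusted variance with equal SDs and rho 0.7–0.3, but only 1.05–1.18 times if the t1 SD is 0.6–0.7 of follow-up and rho 0.3–0.4. The level-contrast variance is 1.10–1.96 times over rho 0.3–0.7. Baseline adjustment is asymptotically never worse than either. Baseline handling is the main component; center is a small one, and its omission is conservative.

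The open random structure matters mainly because it leaves a confirmatory choice to the analyst. Inflated error of the planned gated procedure, bias, or a general shortfall in power has not been shown.

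**What to change.** In Data analyses, replace the model description with one longitudinal model for CAPS-CA-5:

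- time as a factor, with the t1 mean constrained equal across arms (or t2 and t3 as outcomes, with t1 CAPS-CA-5 by time as covariate);
- KIDNET minus TAU effects at t2 and t3;
- center as a fixed effect, with center by time if the joint t1–t3 model is kept, since a center main effect alone leaves the change contrasts untouched;
- one prespecified covariance, unstructured 3 × 3 for the joint model, in place of the either/or.

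Take the joint test, the t2 and t3 contrasts and Cohen's d from this model, so that the gate and the reported effects concern the same quantity. Align Primary outcome with it, and use the same form for the continuous secondary outcomes, which the article already ties to the primary analysis.

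The cost is wording and a few degrees of freedom for center, center by time and the covariance. Every variable is already collected, and the sample size need not change.

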## Discussion

In spite of the known detrimental consequences of trauma originating from war and flight on the mental and physical health of refugees and their integration into the host culture, the evidence regarding effective treatment options for this vulnerable population is very limited [54]. As presented in the literature review in the introduction, research regarding effective interventions for *young* refugees is even sparser. Furthermore, different barriers including language difficulties, fear of stigma, and limited knowledge about treatment options for mental health disorders make it difficult for refugees to seek for help. This is aggravated by bureaucratic obstacles for psychotherapists to receive payments for psychotherapy delivered to refugees with unsecure asylum status, and the required interpreters. Finally, many practitioners are hesitant to deliver evidence-based PTSD treatments due to fears of symptom aggravation or treatment discontinuation [55, 56]. In order to counteract these barriers, and to improve the mental health care for young refugees in the German health care system, systematic studies are urgently required to inform the scientific and clinical community as well as public health decisions.

The lack of systematic studies on effective interventions for war-affected refugee children and adolescents suffering from PTSD might have several reasons. First of all, the group of adolescents might be of greater risk of dropping out of treatment trials due to the developmental tasks in this age period, and unstable mood and motivation [57]. Even more, young refugees face unstable living and housing situations and might be relocated at short notice, making it even more difficult to prevent attrition from the trial. Furthermore, a trial with young refugees requires a close collaboration with, and intense training of, interpreters from different cultures, demanding additional resources from the research team.

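### The 80% power is calculated for a single one-sided t-test, not for the gated interaction procedure that decides superiority, so it is not shown for the confirmatory analysis

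*Protocol article*

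**What the plan says.** Power analysis and sample size calculation: the authors write that "we base the effect size calculation at a conservative estimation of a between-group effect size of" d = 0.6, and then, "with a one-sided alpha level set at 0.05 and a power level of 0.8", that "we need to enroll *N* = 72 subjects (*N* = 36 per group) into the present study". The planned size is 80. The section gives no within-person correlation and does not mention the interaction, the gate or the Holm adjustment. On attrition it cites losses below 5% in earlier studies and adds that, with a mixed model, "all randomized cases can be included in the statistical analyses".

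Data analyses: time, intervention and their interaction are fixed factors, with participants as a random factor (random intercepts, or intercepts and slopes). "The hypothesis that KIDNET is superior to TAU in the treatment of PTSD will be evaluated by the significance test of the interaction effect" of time and intervention. "In case of a significant interaction effect, two planned general linear hypotheses will be calculated as post-hoc tests", comparing the groups at t2 and t3 with one-sided, Holm-adjusted p values. The section closes by setting the level at 0.05 for every analysis, without stating sidedness.

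Discussion, on attrition: "Even more, young refugees face unstable living and housing situations and might be relocated at short notice".

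**The concern.** The calculation and the analysis describe two different tests. With time as a three-level factor (t1, t2, t3), the interaction is a 2-df test without direction, so a one-sided 0.05 cannot be applied to it. It also stands in front of the only directional tests in the plan. A true effect of the planned size must therefore clear two hurdles, and the power statement covers neither.

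If the procedure has less power than stated, the trial may miss an effect it was sized to find. The gate buys nothing in return: Holm over two contrasts already controls the family-wise error at 0.05.

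**Working it through.** **1. The protocol's figure.** Inputs from the sample size section: d = 0.6, one-sided 0.05, 1:1 allocation. Noncentrality = d·√(n/2) with 2n − 2 df. At n = 36 per arm this is 0.6 × √18 = 2.55 on 70 df, giving power 0.810. At n = 35 power is 0.7996, so 36 per arm is the smallest size reaching 80%, and N = 72 is reproduced. At 40 per arm power is 0.845. A two-sided t-test gives 0.709 at 36 and 0.755 at 40 per arm and needs 45 per arm for 80%, so it does not reproduce 72.

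**2. The interaction test.** Assumptions, since the protocol gives none: SD 1 at every visit, constant within-person correlation ρ (compound symmetry, as a random-intercept model implies), no group difference at baseline, d = 0.6 at t2 and t3, complete data.

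Noncentrality λ = (n/2)·Σ(Dj − D̄)²/(1 − ρ), with 2 and 2(2n − 2) df. For D = (0, 0.6, 0.6), D̄ = 0.4 and the sum is 0.16 + 0.04 + 0.04 = 0.24.
- n = 36: λ = 18 × 0.24/(1 − ρ) = 4.32/(1 − ρ), which is 6.17, 8.64, 10.8 and 14.4 at ρ = 0.3, 0.5, 0.6 and 0.7.
- n = 40: λ = 4.80/(1 − ρ), which is 6.86, 9.60, 12.0 and 16.0.

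**3. The gated procedure.** By simulation under the same assumptions (100,000 trials per setting, rounding to within about one point). Holm: the larger of the two contrast statistics is tested at one-sided 0.025, the other then at 0.05. The contrasts are raw group differences at t2 and t3.

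| Power, % | ρ = 0.3 | 0.5 | 0.6 | 0.7 |
|---|---|---|---|---|
| N = 72, interaction alone | 59 | 74 | 84 | 93 |
| N = 72, interaction and at least one contrast | 55 | 67 | 72 | 77 |
| N = 72, at least one contrast, no gate | 88 | 85 | 83 | 82 |
| N = 80, interaction alone | 64 | 79 | 88 | 95 |
| N = 80, interaction and at least one contrast | 61 | 72 | 78 | 82 |
| N = 80, at least one contrast, no gate | 91 | 88 | 87 | 85 |

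At N = 80 the gate costs 91 − 61 = 30 points at ρ = 0.3, 16 at 0.5, 9 at 0.6 and 3 at 0.7. If success requires both time points, the gated procedure gives about 43, 54, 60 and 67% at N = 72 and 50, 61, 67 and 73% at N = 80.

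**4. A fading effect.** With d = 0.6 at t2 and 0.3 at t3, N = 80, interaction plus at least one contrast gives about 47, 57 and 69% at ρ = 0.3, 0.5 and 0.7. Without the gate it is about 79, 77 and 76%, so here dropping the gate helps but does not fully restore 80%.

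**5. Attrition.** Illustration for one arm, with 40 at baseline and 30 followed up. The variance of the mean change from completers alone is 2(1 − ρ)/30. Keeping the baseline-only cases gives (1 − ρ²)/30 + (1 − ρ)²/40. At ρ = 0.5 these are 0.0333 and 0.0313, against 2(1 − 0.5)/40 = 0.0250 with no loss. Baseline-only cases thus cut the inflation from 33% to 25%: not zero, but a minor part of what was lost.

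**The case against.** Several points on the other side stand.

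- **The shortfall is conditional.** A reader might infer that the trial fails to reach 80%. The protocol does not support that, because it gives no correlation. At N = 80 with a sustained effect, the interaction alone passes 80% above ρ of about 0.51, and the full gated procedure does so at about 0.7.
- **The degrees of freedom are an inference.** Fixed factors and contrasts at t2 and t3 point to a three-level time factor, but neither df nor sidedness is stated, and random slopes leave numeric time open. A 1-df two-sided test at N = 80 would have 62, 76 and 85% at ρ = 0.3, 0.5 and 0.6; a one-sided one would have 73, 85 and 91%. The sample size section addresses none of these tests.
- **Direction is handled at the second step.** A reader might infer that a harmful effect could be declared superiority. With KIDNET worse by 0.6 SD (N = 80, ρ = 0.5) the interaction is significant in 79% of simulated trials, but essentially no one-sided contrast is. The sentence tying superiority to the interaction is loose; the procedure as a whole is not misleading.
- **The gate is conservative.** An omnibus test before contrasts does not inflate false claims. It is inefficient, not invalid.
- **Attrition is not called harmless.** The protocol says only that all randomised cases can enter the model, which is true. Its cited loss is under 5%, and 80 × 0.90 = 72, so for the stated t-test the margin already absorbs 10%.

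None of this supplies a power figure for the procedure that will be used.

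**Conclusion.** The point holds in conditional form. N = 72 is correct arithmetic for a test that is not the confirmatory one, and 80% power is not shown for the interaction gate followed by Holm-adjusted contrasts. Under a sustained d = 0.6, compound symmetry and complete data, that procedure is below 80% at N = 72 for every correlation examined (0.3 to 0.7). At N = 80 it is below 80% except towards 0.7, and lower still if the effect fades. These correlations and effect patterns are assumptions. This should be fixed: it weakens the power claim and wastes efficiency, but it does not invalidate the error control or make a false superiority claim likely.

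**What to change.** Choose one of two routes and write it into both statistical sections.

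1. Preferred: remove the interaction gate. Make the two one-sided KIDNET − TAU contrasts at t2 and t3, Holm-adjusted at 0.05, the confirmatory test. State whether success means at least one time point or both, and restate power for that criterion.
2. Alternatively, keep the interaction and restate power for the full gated procedure, giving its degrees of freedom, sidedness, assumed within-person correlation and assumed effect at each follow-up.

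On either route, base the allowance for loss to follow-up on a stated loss rate rather than on the mixed model's ability to include every randomised case.

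Cost: a protocol amendment and an update of the registry record, with the ethics approval and notice to the funder that the protocol's section on safety and ethical aspects requires for such changes. It must precede any unblinded analysis. The first route needs no extra patients under a sustained effect of the planned size with complete data; the second needs none merely to restate power, but may show that N = 80 is short of 80%.
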